### 6.3.3. Economic evaluation

Economic evaluation will be implemented to compare the cost-effectiveness of CMT and UC. The primary economic endpoint will be an incremental cost-effectiveness ratio (ICER) of CMT compared with UC. ICER will be obtained by incremental cost between CMT and UC divided by incremental effectiveness between CMT and UC. Accordingly, additional cost will be calculated when 1 QALY is increased [26]. If predictions about subsequent periods are needed, cost and effectiveness after follow-up period will be extrapolated using regression models or secondary analysis such as decision modelling analysis. The treatment cost of this trial will be calculated by considering the number of treatments and their unit cost, derived from the health insurance cost and the agency cost. QOL inferred from the EQ-5D-5 L will be the primary measurement for the assessment of QALY, and the AUC method will be used [18]. If the total time horizon is more than 12 months, the cost unit will be standardized as the Korean currency (won), and a discount rate of 5% will be applied, based on the guidelines for economic assessment of the Health Insurance Review & Assessment Service. This analysis will be conducted from the societal perspective. Representative values (i.e. mean) of parameters will be used in the baseline analysis. Sensitivity analysis will be carried out in the form of probabilistic sensitivity analysis by using the distribution of all possible parameters and their representative values. In order to confirm the robustness of the analysis results, the probabilistic sensitivity analysis will be performed by setting the range of cost, effect and transition probability variable to 95% confidence interval. The utility weight and the transition probabilities will be analyzed with the triangular distribution and the cost data will be analyzed with the normal distribution for the distribution of the variable. Monte Carlo simulation will be performed 10,000 times and the mean and 95% confidence interval will be calculated. After conducting probabilistic sensitivity analysis, cost-effectiveness acceptability curve will be confirmed [27].

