### 1.2. Economic evaluation

Economic evaluation will be implemented to compare the cost-effectiveness of CMT and UC. The primary economic endpoint will be an incremental cost-effectiveness ratio (ICER) of CMT compared with UC. ICER will be obtained by incremental cost between CMT and UC divided by incremental effectiveness between CMT and UC. Accordingly, additional cost will be calculated when 1 QALY is increased [26]. If predictions about subsequent periods are needed, cost and effectiveness after follow-up period will be extrapolated using regression models or secondary analysis such as decision modelling analysis. The treatment cost of this trial will be calculated by considering the number of treatments and their unit cost, derived from the health insurance cost and the agency cost. QOL inferred from the EQ-5D-5 L will be the primary measurement for the assessment of QALY, and the AUC method will be used [18]. If the total time horizon is more than 12 months, the cost unit will be standardized as the Korean currency (won), and a discount rate of 5% will be applied, based on the guidelines for economic assessment of the Health Insurance Review & Assessment Service. This analysis will be conducted from the societal perspective. Representative values (i.e. mean) of parameters will be used in the baseline analysis. Sensitivity analysis will be carried out in the form of probabilistic sensitivity analysis by using the distribution of all possible parameters and their representative values. In order to confirm the robustness of the analysis results, the probabilistic sensitivity analysis will be performed by setting the range of cost, effect and transition probability variable to 95% confidence interval. The utility weight and the transition probabilities will be analyzed with the triangular distribution and the cost data will be analyzed with the normal distribution for the distribution of the

variable. Monte Carlo simulation will be performed 10,000 times and the mean and 95% confidence interval will be calculated. After conducting probabilistic sensitivity analysis, cost-effectiveness acceptability curve will be confirmed [27].

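### Using the 95% confidence interval as the range of a triangular utility distribution keeps only about 64% of the sampling variance in the probabilistic sensitivity analysis

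*Protocol*

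**What the plan says.** Section 6.3.3 of the protocol names the ICER as the primary economic endpoint and takes effects from the EQ-5D-5L: "QOL inferred from the EQ-5D-5 L will be the primary measurement for the assessment of QALY", by the area-under-the-curve method. For the base case, "Representative values (i.e. mean) of parameters will be used in the baseline analysis". For the uncertainty around it, "the probabilistic sensitivity analysis will be performed by setting the range of cost, effect and transition probability variable to 95% confidence interval". The distributions are then named: "The utility weight and the transition probabilities will be analyzed with the triangular distribution", while "the cost data will be analyzed with the normal distribution". For the output, "Monte Carlo simulation will be performed 10,000 times and the mean and 95% confidence interval will be calculated", and "After conducting probabilistic sensitivity analysis, cost-effectiveness acceptability curve will be confirmed".

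Section 1.2 of the Statistical Analysis Methods at the end of the protocol repeats the rule, including "setting the range of cost, effect and transition probability variable to 95% confidence interval". Neither section describes another analysis of the sampling uncertainty of the ICER.

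**The concern.** A confidence interval is a central part of a sampling distribution, not its full extent. If its limits serve as the minimum and maximum of the draws, the 5% of probability outside is removed. The triangular shape then pulls what remains further towards the centre. A second 95% interval is taken from these draws, so it cannot have 95% coverage for the utility parameters.

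Cost-effectiveness is half of the trial's stated objective. The simulated interval and the acceptability curve are where the protocol expresses uncertainty about the ICER. If the effect component is drawn with too little spread, the curve tends to look more decisive than the data allow, whichever arm it favours. With 80 participants, sampling uncertainty is a main thing this analysis has to convey.

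**Working it through.** The protocol gives no numerical result for the sensitivity analysis, so there is no figure to reproduce. The check works in units of the standard error (SE).

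**Inputs from section 6.3.3:** the range is the 95% confidence interval; utilities are triangular; costs are normal; the central value is the mean; 10,000 draws yield a 95% interval and an acceptability curve. From section 3.5: 40 participants per arm.

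**Assumptions not in the protocol:** the mean is the mode of the triangular distribution; the interval is mean ± a·SE with a = 1.96 unless stated; the share s of net-benefit variance due to effects is unknown and is shown over its range.

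**Utilities, triangular on ±a with mode 0**
- Variance = a²/6 = 1.96²/6 = 0.640, so SD = 0.800 SE.
- The 97.5% point solves (a − x)²/(2a²) = 0.025, so x = a(1 − √0.05) = 1.96 × 0.776 = 1.52.
- The simulated 95% interval is ±1.52 SE, which is 78% of the proper width. Coverage is 2Φ(1.52) − 1 = 0.872.
- With a t-based interval for one arm of 40 (39 df, t = 2.023): 2.023²/6 = 0.68. At 30 df it is 0.70.
- Two moderately asymmetric intervals that were tried gave 0.64 and 0.66.
- By simulation, sums of 2 to 8 independent triangular draws keep 0.64 of the variance, with about 88% coverage.

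**Costs, normal**
- If the interval only supplies the SE, the variance ratio is 1.00.
- If the normal is cut at ±a, the variance is 1 − 2aφ(a)/0.95 = 1 − 2(1.96)(0.0584)/0.95 = 0.759. The 95% interval is ±1.66 SE, with coverage 0.95 × 0.95 = 0.902.

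**Net benefit, costs and effects uncorrelated:** variance ratio = s × 0.640 + (1 − s) × (cost ratio).

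| Effect share s | Costs not cut | Costs cut |
|---|---|---|
| 0 | 1.00 | 0.76 |
| 0.25 | 0.91 | 0.73 |
| 0.50 | 0.82 | 0.70 |
| 0.75 | 0.73 | 0.67 |
| 1 | 0.64 | 0.64 |

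**Acceptability curve:** shown probability = Φ(z/√ratio), where Φ(z) is the true probability. For a true 0.950, z = 1.645:
- s = 0.5, costs not cut: Φ(1.645/√0.820) = 0.965.
- s = 0.5, costs cut: Φ(1.645/√0.700) = 0.975.
- Effects only: Φ(1.645/√0.640) = 0.980.

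**Effect of correlation, if draws are independent:** at s = 0.5 the true net-benefit variance is proportional to 1 − ρ, where ρ is the cost–QALY correlation. The ratio is 0.820/(1 − ρ) with costs not cut, or 0.700/(1 − ρ) with costs cut. It reaches 1 at ρ = 0.18 or ρ = 0.30. At ρ = −0.3 it falls to 0.63 or 0.54.

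**The case against.** The strongest reply is that the loss is established for the triangular parameters only.

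- **Costs.** A reader might infer that every parameter is cut at its interval. The text does not support that. A normal distribution has no minimum or maximum, and the protocol never mentions truncation. The interval may simply supply the SE, in which case costs lose nothing. This stands, and the cost figure has to stay conditional.
- **Size on the curve.** The 0.98 for a true 0.95 is the case where effects dominate. The protocol does not give the effect share, so only a range can be stated. This stands.
- **Direction of the net result.** If costs and QALYs correlate positively and are drawn independently, the simulated net-benefit variance is inflated, which could offset or exceed the loss. This stands as a caution, but it would be one error masking another.
- **Joint sampling.** A reader might infer that the plan draws costs and QALYs independently. The text names marginal distributions and is silent on joint draws, a detail that may sit in an analysis plan not at hand. That silence is no fault here.
- **Transition probabilities.** A reader might see a contradiction with a within-trial ICER. They fit the optional decision-model extrapolation in the same section and are otherwise unused.
- **Another test exists.** Section 6.3.2 compares the area under the curve of each outcome by Student's t-test, and EQ-5D-5L is among the outcomes. That test carries full sampling variance for the effect component, but it does not repair the ICER interval or the acceptability curve.

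None of this rescues the utility draws. Neither the normal-based, the t-based nor the moderately asymmetric intervals tried give a triangular distribution that reproduces the sampling error.

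**Conclusion.** The point holds for the triangular parameters: utilities, and transition probabilities if a model is used. The stated rule keeps about 64% of their sampling variance (about 68% with a t-based interval at 40 per arm). A nominal 95% interval for a utility mean has roughly 87% coverage. This rests on the confidence limits being the minimum and maximum, which is the plain meaning of setting the range, and on the mean being the mode.

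For the economic result as a whole the size is a range. With costs and effects uncorrelated, net-benefit variance is 64% to 100% of its proper value, and 82% or 70% at an equal share. A true acceptability probability of 0.95 is shown as about 0.965 to 0.975 at an equal share, and up to 0.98 if effects dominate. The loss vanishes only if costs are not cut and effects contribute nothing.

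A reader might conclude that the final interval is certainly too narrow and the curve certainly too steep. The protocol does not support that: it gives neither the effect share nor the sign or size of the cost–QALY correlation. The base-case ICER and the primary VAS comparison are not touched.

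**What to change.** In sections 6.3.3 and 1.2, stop using the 95% confidence interval as the bounds of the draws. Either of two changes is enough:

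- Draw each parameter from a distribution whose SD equals its standard error, not bounded by the interval, and state that for costs the interval supplies the SE only.
- Bootstrap patient-level (cost, QALY) pairs within arm. This also preserves the correlation between cost and QALY, and would need to be combined with the multiple imputation planned in section 6.3.2.

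The first corrects the range error with the least change; the second goes further but is not required to correct it. Either costs a rewording in two places and no new data. The downside is that the reported economic uncertainty will generally become wider.

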## 7. Safety Assessment Including Adverse Events

### 7.1. Adverse Event (AE)

#### 1) Adverse Event (AE)

An adverse event refers to any undesirable and unintended sign (e.g., abnormal laboratory test results), symptom, or disease occurring after the procedure during a clinical study. It does not necessarily have to be causally related to the procedure.

#### 2) Serious Adverse Event (SAE)

A serious adverse event during a clinical study of Chuna therapy is defined as an event that meets any of the following criteria:

- Results in death or is life-threatening
- Requires hospitalization or prolongation of existing hospitalization
- Causes persistent or significant disability or impairment
- Constitutes a medically important situation

Even if an event does not meet these criteria, if it is deemed to have a significant impact on the patient's safety and health, the responsible practitioner and related experts will decide whether it should be classified as a serious adverse event and take appropriate action.

### 7.2. Precautions for Use

Practitioners must monitor for adverse events before and after Chuna therapy and take prompt and appropriate measures if any adverse events occur.

#### 7.2.1. Precautions During Chuna Therapy

- Anticipated general side effects, such as mobilization or stimulation of soft tissues around the joints following manual therapy, should be explained to the patient before treatment.
- When performing cervical Chuna therapy, (1) minimize the force of rotational techniques, (2) use techniques that induce segmental rotation with minimal vertebral artery pressure, and (3) avoid unnecessary stress on the vertebral artery and other structures to prevent excessive rotational load on the vertebral artery.
- 

#### 7.3. Assessment Criteria

Adverse events are assessed for their severity and causality using subjective and objective symptoms, physical examinations, and neurological evaluations as needed.

#### 7.4. Assessment Methods

All anticipated phenomena (symptoms and signs, onset date, duration, etc.) resulting from adverse events during Chuna therapy must be recorded in the adverse event report form. Unrecorded events are classified as subjective symptoms. Adverse events are documented in separate case report forms to prevent exposure of patient assignment groups. The severity of symptoms is evaluated in stages based on the evaluation criteria. Causality with the procedure is assessed using the WHO-UMC causality scale, which classifies the relationship into six categories. The severity of subjective and objective symptoms is evaluated using Spilker's three-tier classification.

##### *Spilker's Three-Tier Classification*

- Mild (1): Does not require treatment and does not significantly impair the subject's normal life (function).
- Moderate (2): Significantly impairs the subject's normal life (function), may require treatment, and recovers after treatment.
- Severe (3): Requires intensive treatment due to severe adverse reactions, and may result in sequelae.

##### *Causality with Procedure (WHO-UMC causality scale)*

- Clearly related
- Likely related
- Possibly related
- Unlikely related
- Clearly not related
- Uncertain

The outcome of adverse event follow-up is recorded as:

- Recovered, no sequelae
- Recovered, with sequelae
- Recovering, adverse event persisting, no progression
- Not recovered, adverse event present, progressing
- Death
- Uncertain

Actions taken concerning the clinical study group and control group after adverse events are recorded as:

- Not applicable (does not affect the procedure)
- Temporary suspension of application
- Permanent suspension of application

Additional measures taken beyond planned treatment after adverse events are recorded as:

- None
- Medication
- Hospitalization/prolongation of hospitalization
- Therapeutic or diagnostic procedures
- Others

### **7.5. Interpretation Method**

All adverse events reported during the study period are tabulated, and the incidence rate is calculated. The proportion of patients experiencing adverse events in each group is compared using Chi-square test or Fisher's Exact test.

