| EQ-5D-5L                                                                                    |              |                      | ○                |        |        |        | ○               | ○       | ○       |
| EQ-VAS                                                                                      |              |                      | ○                |        |        |        | ○               | ○       | ○       |
| SF-12                                                                                       |              |                      | ○                |        |        |        | ○               | ○       | ○       |
| Economic evaluation-Medical costs                                                           |              |                      | ○                |        |        |        | ○               | ○       | ○       |
| Economic evaluation-Time costs                                                              |              |                      |                  | ○      |        |        |                 |         |         |
| Economic evaluation-Productivity loss                                                       |              |                      | ○                | ○      | ○      | ○      | ○               | ○       | ○       |
| Adverse events                                                                              |              |                      | ← every visit →  |        |        |        | ○               | ○       | ○       |

\* NRS, VAS K-BDI-2, JFLS, TMJ Range of Motion, PGIC, EQ-5D-5L, EQ-VAS, SF-12, measurements for economic evaluation are conducted during the first visit of the relevant week.

\* During the clinical period, visits scheduled for Week 1 to Week 5 are allowed within ± 3 days of the scheduled visit date, and visits scheduled for 3 months and 6 months after the first visit (visit 2) of Week 1 are allowed within ± 7 days of the scheduled visit date.

\* Subjects selected during the screening visit will begin visit 2 on the same day or within 3 days.

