| Study design           | After voluntarily signing the consent form, the study subjects (or their legal representatives) will be assessed for eligibility to participate in the study. Eligible subjects will be randomly assigned to either the experimental group or the control group. The subjects will receive 8 treatments over 4 weeks (both the experimental and control groups) as per their assigned group. Additionally, there are 3 follow-up visits planned over 24 weeks after registration.                                                                                                                                                                                                                                                                                                                                                                                                                                                                                                                                                                                                                                               |
| Inclusion criteria     | 1) Unilateral or bilateral TMD
2) NRS for TMD pain (more severe side for bilateral TMD) of 4 or above
3) Continuous or intermittent TMJ pain lasting more than 3 months
4) Diagnosed as myofascial TMD, Axis I: Group 1 in RDC/TMD criteria
5) Aged 19–70 years at the signing of the participant agreement form
6) Agreement to participate in the clinical trial, and signing of the agreement form                                                                                                                                                                                                                                                                                                                                                                                                                                                                                                                                                                                                                                                                                                            |

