### 5.5.3. Prohibited Medications

- From study registration until the primary endpoint at week 5 (visit 10), all direct treatments aimed at relieving TMJ pain (e.g., medications, surgeries, other types of acupuncture, and physical therapy) are prohibited for both the clinical study group and the control group. No treatment restrictions are applied during the observation period after the primary endpoint at week 5.

However, during the study period, rescue medication such as acetaminophen (e.g., Tylenol, Acetaminophen tab) will be allowed for all clinical study subjects up to a maximum of 4g per day, and the usage of this medication will be recorded through self-reporting.

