#### 5.5.4. Subject Management During the Follow-Up Period After Treatment Completion

- Clinical study subjects who do not feel completely cured by the final visit or those who experience a recurrence of pain after the treatment completion visit will be allowed to receive treatment at a medical institution of their choice. The details of such treatments will be recorded during the follow-up visits.
- In preparation for any unexpected delayed adverse reactions, subjects will be allowed to seek medical care at any time under the researcher's instructions.

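### Section 7.5 compares adverse events between arms only over the whole study period, without separating the 4-week treatment phase from the unrestricted follow-up after Week 5

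*Protocol*

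**What the plan says.** Section 7.5 holds the only named between-group test of adverse events. It begins "All adverse events reported during the study period are tabulated, and the incidence rate is calculated" and continues: "The proportion of patients experiencing adverse events in each group is compared using Chi-square test or Fisher's Exact test". It gives no onset window and no restriction by causality. The statistical methods text at the end of the protocol adds no adverse-event analysis.

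On exposure, the Summary of Protocol says "The subjects will receive 8 treatments over 4 weeks (both the experimental and control groups) as per their assigned group" and that "there are 3 follow-up visits planned over 24 weeks after registration". The "Adverse events" row of the Timetable shows collection at every treatment visit, at Week 5, at Month 3 and at Month 6.

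On outside care, Section 5.5.3 bars direct treatment of TMJ pain up to the Week 5 primary endpoint and then says "No treatment restrictions are applied during the observation period after the primary endpoint at week 5". Section 5.5.4 adds that patients who are not cured or who relapse "will be allowed to receive treatment at a medical institution of their choice", and that "The details of such treatments will be recorded during the follow-up visits".

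Two other places bear on the analysis. The adverse-events entry in Section 6.2 says that the analysis is mainly of events the researcher suspects to be treatment-related, abnormal laboratory values and serious events. Section 7.4 has onset date recorded and causality rated in six categories.

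**The concern.** The safety question is whether a 4-week course of Chuna manual therapy causes more harm than a 4-week course of usual care. Section 7.5 answers a wider one: whether the arms differ in the proportion of patients with any event over about six months. For most of that time nobody receives study treatment and both arms may have any outside care.

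In the 7.5 proportion, a patient whose only event is an unrelated illness in Month 5 counts the same as a patient with an event after a study session. A patient with an event in both periods counts once, so a later event adds nothing for someone already counted. That mechanism pulls the two proportions together when later risks are equal. If the arms use different amounts or kinds of outside care after Week 5, the later events can also create, hide or enlarge a difference. With 40 patients per arm, there is little power to spare for detecting a difference in harms.

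**Working it through.** The protocol states no adverse-event rate, no safety power and no figure for outside-care use, so there is no planned safety figure to reproduce. The risks below are assumptions that show the mechanism.

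**Share of calendar time after Week 5.** With the 24 weeks of the Summary: (24 − 5)/24 = 19/24 = 79%. With Month 6 taken as 26 weeks: (26 − 5)/26 = 21/26 = 81%.

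**Dilution.** Let p be the risk of an event up to Week 5 and q the risk of an event afterwards, taken as independent. The whole-period risk is P = 1 − (1 − p)(1 − q). With the same q in both arms,

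P₁ − P₂ = (1 − p₂)(1 − q) − (1 − p₁)(1 − q) = (p₁ − p₂)(1 − q).

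So the risk difference shrinks by exactly 1 − q. With assumed risks to Week 5 of 30% (Chuna) and 5% (usual care), 40 per arm, and Fisher's exact test at two-sided 0.05 by full enumeration:

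| Later risk q, both arms | Whole-period risks | Difference (points) | Power |
|---|---|---|---|
| none (Week 5 window only) | 30% and 5% | 25 | 82% |
| 10% | 37% and 14.5% | 22.5 | 56% |
| 20% | 44% and 24% | 20 | 38% |
| 30% | 51% and 33.5% | 17.5 | 29% |
| 50% | 65% and 52.5% | 12.5 | 15% |

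With smaller assumed risks of 20% and 5%, power is 41% in the Week 5 window and falls to 24%, 15%, 11% and 7% for the same values of q.

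**Distortion when later risks differ by arm.**
- No treatment-period difference (10% in each arm), later risks 10% (Chuna) and 30% (usual care): 1 − 0.9 × 0.9 = 19% and 1 − 0.9 × 0.7 = 37%. Fisher's test is significant in 35% of trials although the treatment-period risks are equal.
- Treatment-period risks 30% and 5%, later risks 10% (Chuna) and 30% (usual care): 1 − 0.7 × 0.9 = 37% and 1 − 0.95 × 0.7 = 33.5%. A 25-point difference becomes 3.5 points.
- The same treatment-period risks with the later risks exchanged: 1 − 0.7 × 0.7 = 51% and 1 − 0.95 × 0.9 = 14.5%. The difference becomes 36.5 points.

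The last two lines show that the distortion can run either way.

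**The two descriptions of the analysis.** Section 6.2 gives priority to suspected-related and serious events. Section 7.5 tests the proportion with any event. These are different sets of events, and neither section says over what time they are counted.

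**The case against.** The strongest defence is Section 6.2. It makes suspected treatment-related and serious events the main content of the analysis, and 7.4 has causality rated against the procedure. An event from outside care can be rated as unrelated, so a reader who infers that such events are simply charged to the randomised arm goes too far. That stands. But 7.5 does not carry the restriction into its test, 6.2 sets no window, and relatedness is the researcher's judgement in a trial whose practitioners cannot be blinded (Section 5.2.2). Onset date is a less subjective filter.

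A whole-period comparison by randomised arm is also a legitimate summary of what follows from assignment, and it captures the delayed reactions that 5.5.4 anticipates. That stands too, and is why the pooled comparison should be kept.

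The calendar share overstates where events are likely to be picked up. Of 11 treatment and follow-up contacts (8 + 3), 9 fall by Week 5. So the 80% describes time at risk and says nothing about the share of events captured.

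Finally, a treatment-emergent window is often left to a statistical analysis plan, and one may exist. The point here is narrower: 7.5 itself fixes a whole-period test, and that test does not match the focus in 6.2.

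**Conclusion.** The point holds as a matter of analysis choice. The only named between-group test of adverse events runs over a period of which about 80% lies after Week 5, under unrestricted outside care, and it does not match the focus that Section 6.2 gives. The contraction by 1 − q is exact if the later risk is equal in both arms and independent of the earlier one. Every event rate used above is assumed, so the real loss could be small or large.

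A reader might infer that the pooling makes Chuna look safer. The documents do not support that. Equal background risk pulls towards no difference, but the effect of outside care depends on which arm seeks more of it and what it is. Sections 5.5.3 and 5.5.4 give both arms the same freedom, and no figure by arm is given. The direction is unknown.

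**What to change.** In Section 7.5:

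1. Add a between-group comparison of events with onset from the first study treatment to the Week 5 visit, and name it as the comparison that addresses harms of the 4-week treatments.
2. Tabulate events with onset from Week 5 to Month 6 separately by group, and flag those that began after recorded outside TMJ treatment.
3. Keep the pooled 6-month comparison, so that delayed events stay visible.
4. Reconcile 7.5 with Section 6.2 by showing all events and suspected-related events in each period.

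The cost is a few sentences and one or two extra tables. Outside treatments are already recorded under 5.5.4, and onset date under 7.4. Because 7.4 words its recording rule for Chuna therapy, confirm that the form also takes the onset date in the usual-care arm, and that outside treatments are dated. The drawback is that delayed events sit outside the Week 5 comparison and are seen only in the follow-up and pooled tables.
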